**16.2. Is there a sample size/power calculation?**

☐ No ☒ Yes: *If yes, describe the calculation and the scientific rationale, and, if applicable, by site and key characteristics such as participant demographics.*

To compare the primary outcome of total kcals purchased across the seven groups, we determined that a sample of 4,900 participants (700 per group) would provide at least 80% power to detect an 18-kcal difference between each group, assuming an alpha of 0.05. This estimate is based on effect sizes found in our previous labeling research. It is typical to exclude a small number of participants in online studies (e.g., for failing data integrity check questions), so we will recruit 5,000 participants. Qualtrics has confirmed that this will be feasible given our inclusion criteria.

**17. Costs and Compensation** ☐ N/A. *Skip to next section.*

**17.1. Identify any costs that participants may incur during the study, including transportation costs, childcare, or other out-of-pocket expenses.**

None

**17.2. Identify remuneration that participants may receive during the study. Specify the amount, timing of disbursement, and method (e.g. money, gift cards, in-kind, incentives, raffles, and transportation). Describe how compensation will be calculated and paid if a participant withdraws. If any participant will receive a single payment more than \$100, or \$600 or more in one calendar year, refer to [Harvard University Financial Policy on Human Subject Payments](#).**

Participants will receive a \$5 gift card at the end of their participation in the study, dispensed through Qualtrics via participant emails. They will receive compensation regardless of whether they stop the study early.

**18. Sharing Study Results** ☐ N/A. *Skip to next section.*

**18.1. Describe the plan to share study results with individual participants, the participant group/community, and/or others.**

Results will be published in a scientific journal, and will be shared via webinar with the FDA.

**19. Research Related Injuries** ☒ N/A. *Skip to next section.*

19.1. Describe plans for medical care and compensation for research-related injuries.

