**Label Randomization.** Caregivers will be randomized using simple randomization via the Qualtrics platform to see fruit drinks in our online store and survey with one of the following seven label conditions (**Appendix B**). The first condition (*claim & imagery*, control) will represent the status quo and contain a 100% Vitamin C claim and fruit imagery. Conditions 2-4 will involve the removal of package elements for fruit drinks high in added sugar (“high sugar”,  $\geq 10\text{g/serving}$ , 20% DV): Condition 2 (*imagery only*) will have fruit imagery but no 100% Vitamin C claim on high-sugar fruit drinks; Condition 3 (*claim only*) will have a 100% Vitamin C claim but no fruit imagery on high-sugar fruit drinks; and Condition 4 (*no claim or imagery*) will feature no imagery or claims on high-sugar fruit drinks. Conditions 5-7 will involve the addition of package elements. Condition 5 (*imagery, claim, & text % fruit juice disclosure*) will show a text description of the percent fruit juice in each fruit drink, to see if it changes the effects of the claim and imagery. The sixth (*imagery, claim, & added sugar warning*) and seventh conditions (*imagery, claim, & added sugar warning w/teaspoons of sugar*) will test the effects of added sugar warnings.

**Primary Outcomes:** The primary outcomes will be total calories and grams of added sugar purchased in the online store task (averaged by condition). We will also examine the percentage of people in each condition that purchased a drink high in added sugars ( $>20\%$  DV) for their child, and the percentages that chose each category of drink (fruit drinks, 100% juice, etc).

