**16. Data/Statistical Analyses Plan**

**16.1. Describe plans for analysis (including the statistical method, if applicable).**

Linear regression will be used to examine mean total calories and grams of added sugar purchased between our experimental groups. Logistic regression will be used to compare proportions in each condition that chose different beverage types. Because of the randomized design, the only covariates we will control for will be purchasing frequency (for secondary outcomes), and those that may by chance significantly differ among the groups. A Bonferroni-Holm correction will be used to control for multiple comparisons. In secondary analyses we will stratify the main effects by SNAP/WIC status, race/ethnicity, household income, and frequency of child fruit drink consumption.

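### The 80% power in section 16.2 is quoted at alpha 0.05 with no SD and no multiplicity allowance, although section 16.1 tests with Bonferroni-Holm; read as pairwise, it falls to about 56% for six contrasts with control

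*Protocol*

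**What the plan says.** Section 16.2 bases the sample size on total kcal purchased. With 4,900 participants, 700 in each of seven groups, the design "would provide at least 80% power to detect an 18-kcal difference between each group, assuming an alpha of 0.05". The only support given is that "This estimate is based on effect sizes found in our previous labeling research". No SD, test or sidedness is stated.

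Section 16.1 plans linear regression for mean calories and mean grams of added sugar, and adds: "A Bonferroni-Holm correction will be used to control for multiple comparisons". It does not list the comparisons covered.

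Section 5.6 sets out seven label conditions, of which the first (claim and imagery) is labelled the control. It also says: "The primary outcomes will be total calories and grams of added sugar purchased in the online store task".

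**The concern.** The power is quoted at one threshold and the tests will be run at stricter ones. Under Holm, the smallest p-value in a family of m tests is compared with 0.05/m, the next with 0.05/(m-1), and so on. With seven conditions, the smallest natural family on one outcome is the six contrasts with control, so the first threshold is 0.05/6 = 0.0083. The wording "an 18-kcal difference between each group" could also be taken to mean all pairs, of which there are 7 x 6 / 2 = 21.

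Interpretation is what is at stake. Sections 13.1 and 18.1 say that the results are meant to inform federal regulation and will be presented to the FDA. If a label condition shows no significant effect, a reader who relies on at least 80% power may take that as evidence against an 18-kcal effect, although the corrected test might often miss one. Type I error is not in question, since Holm controls it.

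**Working it through.** **Inputs.** From section 16.2: difference 18 kcal, 700 per group, power at least 80%, alpha 0.05. From section 16.1: Holm. From section 5.6: seven conditions, one of them the control, and two primary outcomes. Assumed because not stated: two-sided tests, a normal approximation, and 0.05 applied to each pairwise comparison.

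**Step 1: the plan's own figure.** Without an SD it cannot be checked independently, only solved backwards. For exactly 80% power,

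SD = 18 / [(1.960 + 0.842) x sqrt(2/700)] = 18 / (2.802 x 0.05345) = 120.2 kcal.

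This returns 700 per group by construction. Because the plan says at least 80%, 120 kcal is an upper limit on this reading.

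**Step 2: power at the first Holm step.** The standard error of a difference is 120.2 x 0.05345 = 6.425 kcal, and 18/6.425 = 2.802. For m tests,

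power = Phi(2.802 - z(1 - 0.05/(2m))).

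The SD has cancelled, so the drop from 80% does not depend on its value. The difference detectable with 80% power is [z(1 - 0.05/(2m)) + 0.842] x 6.425.

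| Holm family | m | Critical z | Power for 18 kcal | Detectable at 80% |
|---|---|---|---|---|
| One comparison (as in 16.2) | 1 | 1.960 | 80.0% | 18.0 kcal |
| Six conditions vs control, kcal | 6 | 2.638 | 56.5% | 22.4 kcal |
| All pairs, kcal | 21 | 3.038 | 40.7% | 24.9 kcal |
| Six vs control, both outcomes* | 12 | 2.865 | 47.5% | 23.8 kcal |
| All pairs, both outcomes* | 42 | 3.241 | 33.0% | 26.2 kcal |

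*The protocol does not say that one family spans both outcomes.

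**Step 3: does stepping down recover the loss?** These figures are floors, because later Holm steps use looser thresholds. In a simulation of the full procedure (40,000 runs, SD 120.2), power for one given contrast with control was:

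- only that condition differs from control: 56.5% (six contrasts), 42% (21 pairs);
- all six conditions differ from control by 18 kcal: 67% (six contrasts), 42% (21 pairs).

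**Step 4: what SD would rescue the statement?** If 0.05 is family-wise, 80% power at the first step needs SD <= 18 / {[z(1 - 0.05/(2m)) + 0.842] x 0.05345}. That is 96.8 kcal for m = 6, 90.8 for m = 12, 86.8 for m = 21 and 82.5 for m = 42.

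**The case against.** The strongest reply is that section 16.2 never calls its alpha unadjusted. Holm also controls error at 0.05, so the figure could be family-wise; with an SD of about 97 kcal or less, six contrasts would have 80% power. The 120-kcal SD comes from assuming the reading in dispute. This stands in part: with no SD, the family-wise reading cannot be excluded. But nothing in the section points to it. An effect described as a difference between groups, with a plain 0.05, reads most naturally as pairwise and unadjusted.

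A second reply is that section 16.2 speaks of comparing the outcome across the seven groups, which could mean an omnibus F test. If 18 kcal separates the two extreme groups and the rest lie midway, the back-solved SD is about 91 kcal, and first-step power for that pair is 85% (m = 6), 80% (m = 12), 74% (m = 21) or 67% (m = 42). If only one group differs, the SD is about 119 kcal and the m = 6 figure is 57%. If three groups differ from the other four, the SD is about 169 kcal and it is 26%. So this reading can help or hurt, and section 16.1 plans regression with Holm and names no omnibus test.

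A third reply is that the Holm family belongs in the statistical analysis plan, which is not shown. That is fair for the ranking of the two primary outcomes and for a power figure for added sugar; their absence here is not a fault. It does not cover a power figure that the protocol itself states at an alpha its own procedure does not appear to use.

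**Conclusion.** The point holds conditionally. On the natural pairwise reading of section 16.2, the stated 80% is not the power of the planned test. It is about 56% at the first Holm step for six calorie contrasts with control, rising to about 67% per contrast if every condition differs from control by 18 kcal, and about 41% for all 21 pairs. This rests on two-sided tests and on 0.05 being per comparison. The figures are lower limits, both because Holm steps down and because the plan says at least 80%.

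A reader might go further and infer that the design has only 33% to 56% power over seven arms and two outcomes. The documents do not support that. Section 16.1 does not put both outcomes in one family, and the 56% is for calories alone; with both outcomes in the family, the first-step figures are 33% to 47%. Nor is there a proven miscalculation, since without an SD no stated figure can be shown to be wrong.

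**What to change.** In section 16.2:

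- State the SD of kcal purchased and whether the test is two-sided.
- Name the Holm family that the power refers to, for example the six other conditions against the claim and imagery control on calories.
- Restate the power at that alpha. Suggested wording, if the SD is 120: *With 700 per group, SD 120 kcal and Holm over six contrasts with control, power for an 18-kcal difference is at least 56%, and the difference detectable with 80% power is 22.4 kcal.*
- If 0.05 was already family-wise, say so and give the SD that supports it (about 97 kcal or less for six contrasts).

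This changes wording only. No extra recruitment is asked for. The cost is a less favourable stated power, unless the SD turns out to support the present figure.

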## 20. Reportable Events

20.1. Outline plans for communicating reportable events to the IRB, Sponsor, or others as applicable (e.g., adverse events, unanticipated problems involving risks to participants or others, breach of confidentiality).

Reportable events will be reported within 5 days of the PI finding out in accordance with OHRA policies.

## 21. Regulatory Compliance

21.1. Describe plans for monitoring regulatory compliance. The monitoring plan should include how you will ensure proper record keeping, retention of required regulatory documents and participant files, and adherence to the IRB-approved protocol and/or IRB policies and procedures. Monitoring plans should describe 1) who is responsible for file maintenance, 2) what will be maintained, 3) how often files will be reviewed and using what method, and 4) where documentation will be retained (for both Regulatory Documents and Participant files).

The study coordinator will be responsible for monitoring regulatory compliance to ensure proper record keeping and retention of required regulatory documents, including the research team CVs and CITI certifications, and IRB submissions (which will also be kept electronically using ESTR). We will use QIP's "CHECKLIST: Investigator Quality Improvement Assessment" to conduct internal checks on a bimonthly basis.

## 22. Data or Biospecimen Sharing ☒ N/A. Skip to next section.

If you plan to establish a repository, please submit a separate application using the [HLC Repository Protocol Template](#).

22.1. Describe the plan to send data/specimens to research collaborators outside of Harvard.

☐ N/A

22.2. Describe the plan to receive data/specimens from collaborators outside of Harvard.

☐ N/A

## 23. Clinical Trials ☒ N/A. Skip to next section.

Complete this section for clinical trials, including [NIH funded clinical trials](#) or [applicable clinical trials \(ACT\)](#) under the [FDA Amendments Act](#). To determine if a study meets the definition of a clinical trial, follow the guidance in the "Preparing the Research Protocol" section of the Investigator Manual.

23.1. Describe how this study meets the definition of a clinical trial.

23.2. Describe plans for registering this project in a clinical trials registry, e.g., [clinicaltrials.gov](#). If available, provide the registry record number.

23.3. Describe plans for posting the clinical trial consent form on a publicly available federal website per federal requirements in the Common Rule (45§46.116(h)).

## 24. Device *This section should be completed if the study involves the use of any device on/in/with human subjects, and/or the use any device utilizing human specimens, which meets [the FDA definition of a medical device](#).* ☒ N/A. Skip to next section.

24.1. Describe the device, including the generic or common name, brand name (if applicable), purpose, function/operation, and whether it is an implant. Indicate who is providing this device for research use.

24.2. Indicate the FDA status of the device as it is being used for the proposed research:

☐ FDA-approved device being used "on-label" (i.e., FDA-approved purpose, population, manner).

☐ FDA-approved device that is being used "off-label" (i.e., for a different purpose, population, or in a different manner than approved).

☐ Not approved by the FDA.

24.3. Indicate the IDE Status of this device:

☐ The use of this device has an IDE.

- ☐ The use of the device qualifies for an Abbreviated IDE.  
☐ The use of the device is exempt from the IDE requirements.

**24.4. Has the FDA made a determination as to whether the device is Significant Risk or Non-Significant Risk?** ☐ No ☐  
**Yes:** *If yes, indicate the FDA's determination.*

**24.5. Describe plans for storage control, and dispensing of the product so that (1) only authorized investigators will use the product; (2) the product will only be used in participants who have provided consent, and (3) there will be documented tracking of each product, including unique identifiers and any return/disposal.**

**25. Drug/Biologic** *This section should be completed if the study involves the use of any drug/biologic on/in/with human subjects which meets [the FDA definition of a drug/biologic](#). ☒ N/A. Skip this section.*

**25.1. Describe the drug or biologic, including the generic or common name, brand name (if applicable), dosing, route of administration, number of doses, timing of administration. Indicate who is providing the drug, biologic, supplement for research use.**

**25.2. Indicate the IND Status of this drug or biologic and who holds the IND: (select one)**

|                          |                                                                 |
|--------------------------|-----------------------------------------------------------------|
|  | There is an IND approval from the FDA for the use of this item. |
|                          | The IND is held by:                                             |
|                          | The IND number is:                                              |
|  | An IND application has been, or will be, submitted to the FDA.  |
|                          | The IND will be held by:                                        |
|                          | The IND number is:                                              |
|  | An IND approval is not required.                                |

**25.3. Describe how dispensing, delivery and administration will be performed, and by whom. Include information about control (e.g., locked storage), tracking (e.g., lot number, returned pills), documentation, storage, and return/disposal.**
